### Assignment of interventions (randomisation and allocation)

Sequence Generation: A randomisation sequence will be generated using variable block sizes (2, 4, 6, or 8) with a 1:1 allocation ratio by a statistician independent of the clinical team, using R studio statistical software with a pre-specified random seed (20221023).

Allocation Concealment Mechanism: Due to the nature of the intervention, allocation concealment from the participants and the clinicians performing the intervention is not possible. However, the randomisation sequence will be managed by personnel not involved in patient recruitment or assessment to prevent foreknowledge of allocation before eligibility is confirmed.

Implementation: Once a participant completes the run-in period, meets all eligibility criteria, and provides final consent for randomisation, the study coordinator will contact the central randomisation service/personnel to obtain the treatment allocation according to the generated sequence.

#### Sample size

Based on previous research, the healing rate in the SOC group is approximately 47% (21). Our institutional pre-experiment (pilot study) of DFU patients receiving continuous regional block showed that approximately 80% of participants achieved complete wound closure within 12 weeks; thus, we hypothesized that CPIPB + SOC will increase the 12-week healing rate to approximately 80%. To detect this difference with 90% power (β=0.10) at a one-sided significance level of α=0.05, 35 participants are required per group. Accounting for an estimated 10% dropout rate, a total of 78 participants (39 per group) will be recruited.

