### Statistical methods

The primary analysis will be conducted on the intention-to-treat (ITT) population, defined as all randomised participants regardless of adherence or withdrawal.

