#### Primary outcome analysis

The proportion of participants achieving complete ulcer healing at 12 weeks will be compared between the CPIPB+SOC group and the SOC group using a chi-square test or Fisher’s exact test, as appropriate. Odds ratios (OR) with 95% confidence intervals (CI) will be calculated using logistic regression, potentially adjusting for important baseline covariates (e.g., baseline ulcer area, UTC grade, duration of the ulcer, and baseline perfusion status (TcPO2)). Furthermore, to explore potential variations in treatment response, prespecified subgroup analyses will be conducted based on baseline ulcer size, UTC grade, and baseline perfusion status.

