#### Secondary outcome analysis

Time-to-event outcomes (time to healing, time to recurrence) will be analysed using Kaplan-Meier curves and compared using the log-rank test. Hazard ratios (HR) with 95% CIs will be estimated using Cox proportional hazards regression, adjusting for covariates.

Continuous outcomes (e.g., percentage area reduction, change in VAS, change in TcPO2, Wound-QoL scores) will be compared using independent t-tests or Mann-Whitney U tests, depending on data distribution. Analysis of covariance (ANCOVA) may be used to adjust for baseline values.

Binary secondary outcomes (e.g., proportion achieving ≥50% area reduction, infection incidence) will be compared using chi-square or Fisher’s exact tests, with ORs and 95% CIs from logistic regression.

Adverse event rates will be summarized descriptively and compared using Fisher’s exact test.

To address missing primary and secondary outcome data, multiple imputation by chained equations (MICE) will be performed as a sensitivity analysis under the missing-at-random (MAR) assumption. No interim analysis is planned for this study due to the relatively modest sample size (n=78). To control the family-wise error rate, the Bonferroni correction will be applied to adjust p-values for multiple comparisons among secondary outcomes. All statistical tests will be two-sided with a significance level set at P < 0.05. Statistical analysis will be performed using SPSS version 18.0 (SPSS, Inc., USA) and GraphPad Prism version 8.2.

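### The trial is sized with a one-sided 5% test but analysed with a two-sided 5% test, so the stated 90% power is about 83%

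*Protocol article*

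**What the plan says.** The Sample size section assumes 12-week healing of about 47% under standard of care and about 80% with CPIPB added. It then states: "To detect this difference with 90% power (β=0.10) at a one-sided significance level of α=0.05, 35 participants are required per group". Recruitment follows from that figure: "Accounting for an estimated 10% dropout rate, a total of 78 participants (39 per group) will be recruited".

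The Primary outcome analysis section compares the two healing proportions "using a chi-square test or Fisher’s exact test, as appropriate", and reports odds ratios with 95% confidence intervals. It does not say whether the test is one- or two-sided. The sidedness is given in the closing paragraph of the statistical section, printed under Secondary outcome analysis: "All statistical tests will be two-sided with a significance level set at P < 0.05". The primary population is intention-to-treat, "defined as all randomised participants regardless of adherence or withdrawal".

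**The concern.** The sample size section and the analysis section set different rejection rules for the same comparison. A one-sided 5% test needs a standardised difference of 1.645 in favour of CPIPB; a two-sided 5% test needs 1.960. A sample size that just reaches 90% power at the lower threshold cannot reach it at the higher one.

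Two things are at stake:

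- **Reading a neutral result.** It would be taken as coming from a trial with a 10% chance of missing the planned effect, when the analysis rule gives a larger chance.
- **The success criterion.** A result favouring CPIPB with a two-sided p-value between 0.05 and 0.10 is positive under the sample size section and negative under the analysis section. The one-sided 5% rule allows a 5% false-positive rate in the favourable direction, twice the 2.5% of the two-sided rule. In an open-label trial this should be settled in the text before results are known.

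**Working it through.** **Inputs, all from the protocol article**

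- p1 = 0.47 (standard of care), p2 = 0.80 (CPIPB plus standard of care), difference d = 0.33: Sample size
- 90% power, one-sided α = 0.05, 35 per group, 10% dropout, 39 per group recruited: Sample size
- 1:1 allocation: Assignment of interventions
- Two-sided 0.05 for all tests: closing paragraph of the statistical section
- Chi-square or Fisher's exact test: Primary outcome analysis

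**Formula** (two proportions, pooled variance under the null, no continuity correction)

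n per group = [z_α √(2 p̄ q̄) + z_β √(p1q1 + p2q2)]² / d²

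- p̄ = (0.47 + 0.80)/2 = 0.635 and q̄ = 0.365, so √(2 × 0.635 × 0.365) = √0.46355 = 0.6808
- p1q1 + p2q2 = 0.2491 + 0.1600 = 0.4091, square root 0.6396
- z_β = 1.2816 for 90% power; d² = 0.1089

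**Step 1: reproduce the protocol's figure (one-sided, z_α = 1.6449)**

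n = (1.6449 × 0.6808 + 1.2816 × 0.6396)² / 0.1089 = (1.1199 + 0.8197)² / 0.1089 = 34.5, so 35 per group. Power at 35 is 90.3%. With dropout, 35/0.9 = 38.9, so 39 per group and 78 in total. The protocol's numbers are reproduced exactly.

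**Step 2: the same formula with the planned test (two-sided, z_α = 1.9600)**

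n = (1.9600 × 0.6808 + 0.8197)² / 0.1089 = (1.3344 + 0.8197)² / 0.1089 = 42.6, so 43 evaluable per group. With dropout, 43/0.9 = 47.8, so 48 per group and 96 in total.

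**Step 3: power of the planned test at the planned size**

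Power = Φ{[d√n − z_α √(2 p̄ q̄)] / √(p1q1 + p2q2)}

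- n = 35: (0.33 × 5.916 − 1.3344)/0.6396 = 0.966, power 83.3%
- n = 39: (0.33 × 6.245 − 1.3344)/0.6396 = 1.136, power 87.2%

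**Step 4: cross-check by exact enumeration**

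The binomial probabilities of every 2×2 table in which the two-sided 5% test rejects in favour of CPIPB were summed.

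| Evaluable per group | Normal approximation | Exact, chi-square | Exact, Fisher |
|---|---|---|---|
| 35 | 83.3% | 84.0% | 77.5% |
| 39 | 87.2% | 87.6% | 81.3% |

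**Step 5: could another two-sided formula give 35?**

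No. For 90% power at two-sided 5%, the unpooled formula gives 40, the arcsine 43, the pooled 43 and the continuity-corrected 49 per group.

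**The case against.** The strongest reply is that 83% is the low end. The primary population is everyone randomised, 39 per group are recruited, and the protocol tries to obtain a final assessment from dropouts. At 39 per group the two-sided power is about 87%, and the unpooled formula gives 89.7%. This stands in part: 87% belongs in the corrected text. But the protocol states its own 90% at 35 per group, so 83% is the like-for-like figure. The 87% also needs every randomised participant to have an outcome at the planning rates, while the protocol itself plans for 10% dropout. The 89.7% comes from a formula that does not reproduce the protocol's 35.

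Other points on that side:

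- *The arithmetic is right for the one-sided test that the section openly declares.* True. The fault is the conflict with the analysis rule, not a slip in calculation.
- *The two-sided sentence is printed under the secondary outcomes.* True, and the primary section is silent on sidedness. But the sentence covers all tests, and its paragraph also deals with missing primary data, interim analysis and software. The 95% intervals for the primary odds ratio also correspond to a two-sided 5% test.
- *Fisher's test is unlikely to be used.* Fair. At the planning rates the smallest expected cell is 35 × 0.365 = 12.8, so chi-square is the likely test. The Fisher figures are only a lower bound.
- *A positive result stays valid.* Yes, provided the two-sided rule is the one applied.

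**Conclusion.** The concern holds, and the power statement is wrong as written. Under the protocol's own two-sided 5% rule, 35 evaluable participants per group give about 83% power (exact chi-square 84%) for 47% against 80%, a shortfall of about 7 points. The chance of missing the planned effect is about 17%. With outcomes for all 39 per group, power is about 87% (exact chi-square 88%), still about 3 points short.

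These figures take the protocol's two healing rates as given, assume 1:1 allocation and an unadjusted chi-square test without continuity correction, and read the two-sided sentence as covering the primary test. Nothing in the article says otherwise.

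**What to change.** Keep the two-sided 5% test. In Sample size, delete the one-sided statement and restate the power, for example:

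> With 35 evaluable participants per group, a two-sided 5% chi-square test has about 83% power to detect 47% versus 80% healing at 12 weeks (about 87% if all 39 per group have an outcome).

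It would help to add to Primary outcome analysis that the primary test is two-sided at 5%, so that the rule no longer rests on a sentence under the secondary outcomes.

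The cost is one rewritten sentence, one optional short addition, and a less favourable power figure. Recruitment stays at 78. Keeping the 90% claim with the two-sided test would instead require 43 evaluable per group, or 96 in total after 10% dropout; that increase is not requested here.

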#### Recruitment

Participants will be recruited from patients attending the DFU clinics. Potential participants meeting initial screening criteria will be approached by the study team, provided with information, and invited to provide informed consent for the run-in period and potential randomisation. Strategies to enhance recruitment include clinician education and regular screening logs.

### Quality control

To uphold the integrity of clinical trials, both sponsors and participants must adhere to established standard operating procedures (SOPs) for robust quality control and the effective implementation of the overarching quality assurance system. All observational data and emergent findings generated during the trial necessitate rigorous verification to substantiate data reliability. Furthermore, it is imperative that all conclusions drawn from clinical trial results are demonstrably rooted in and supported by the primary data. Continuous quality control mechanisms should be integrated throughout the entire data processing pipeline, ensuring that all recorded information is both dependable and accurately handled.

### Monitoring

The sponsor designates a monitor responsible for conducting routine on-site visits to the investigational site. These visits are essential for verifying strict adherence to all aspects of the study protocol and for cross-referencing original data against the Case Report Form (CRF) to confirm data consistency.

### Interventions

#### Intervention group (CPIPB + SOC)

Participants randomised to this group will receive SOC (detailed below) combined with the CPIPB procedure.

##### CPIPB procedure

The specific treatment process includes patients undergoing parasacral ischial plane catheterization by the same treatment team in accordance with the study method proposed by Ye et al. (17).

##### Infusion

Post-procedure, a continuous infusion of 0.2% ropivacaine is delivered at 5 mL/h via an infusion pump for 14 days. This specific regimen is chosen based on our previous clinical feasibility and dose-finding trials (17, 19); this concentration and rate selectively block sensory and sympathetic fibres while sparing motor function, thereby preserving patient mobility and enabling essential rehabilitation. Delivering 10 mg of ropivacaine per hour (5 mL/h) is also well below the established systemic toxic threshold (0.6 mg/kg/h) (22), ensuring long-term safety. The 14-day infusion duration is derived from our pilot data and preclinical evidence (19), which indicate that a minimum of 10 to 14 days of sustained regional sympathetic blockade is required to downregulate inflammatory mediators, initiate microvascular remodelling, and promote robust local angiogenesis.

##### Control group (SOC)

Participants randomised to this group will receive standard of care (SOC) alone. To minimize performance bias and ensure study reproducibility, the SOC is highly standardized and encompasses several key clinical dimensions. First, glycaemic management will be overseen by a consulting endocrinologist, targeting an HbA1c < 8.0%, fasting blood glucose < 7.0 mmol/L, and postprandial blood glucose < 10.0 mmol/L (23). Second, sharp debridement of hyperkeratotic margins and non-viable tissues will be performed weekly by a dedicated, trained wound care podiatrist or nurse as clinically indicated. Third, wound dressings will be selected based on wound characteristics, utilizing either standard plain Vaseline gauze as specified in the protocol, or standardized moisture-retentive dressings, applied and changed every 2 to 3 days, or daily if clinically necessary. Fourth, standardized offloading interventions will be tailored to the anatomical location of the ulcer and patient compliance, including the use of custom-molded therapeutic footwear, felt-on-foam pressure-relieving pads, or non-removable knee-high walkers (24). Fifth, local or systemic infections will be managed strictly according to standard protocols; systemic antibiotic therapy will only be initiated if the patient exhibits clear clinical signs of infection in accordance with the IWGDF/IDSA guidelines, whereas prophylactic antibiotics are strictly prohibited (25). Finally, participants will attend regular, scheduled follow-up visits for comprehensive and standardized wound assessment and care.

### Concomitant medications and care

All participants will continue necessary medications for comorbidities (e.g., diabetes, hypertension, dyslipidaemia). Use of systemic analgesics will be recorded. Both groups will receive education on DFU prevention and self-care.

### Outcomes

#### Primary outcome

The primary study end point was the percentage of ulcers in each group achieving 100% healing at 12 weeks. Complete healing is defined as 100% re-epithelialization without drainage or dressing requirements, confirmed at two consecutive visits 2 weeks apart by an independent, blinded wound specialist. To ensure objective evaluation, wound areas will be traced and verified using computerized planimetry (ImageJ) on standardized digital photographs (taken with fixed distance, positioning, and illumination). These photographs will be securely archived and cross-checked by a central, blinded adjudication committee of two senior plastic surgeons.

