### Participant timeline

Participants will attend visits at baseline (week-2 and Week 0, randomisation), Week 2, Week 4, Week 6, Week 8, Week 12 and year 1. The CPIPB infusion runs for the first 14 days (Week 0 to Week 2). Data collection points for specific outcomes are outlined in the schedule of assessments (**Table 1**).

**Table 1 T1:** Schedule for data collection, the process of the assessments per visit.

Measures	Baseline	Intervention phase					
Time(weeks)	-2-0	2	4	6	8	12	1 year
Informed consent	√						
Demographics and Past medical history	√						
Physical examination	√	√	√	√	√	√	√
Laboratory Tests	√	√				√	√
Hemodynamic Tests	√	√	√	√	√	√	√
Electrocardiogram	√						
Ascertainment of Inclusion and Exclusion Table	√						
Routine follow-up measurement table	√	√	√	√	√	√	√
Adverse events	√	√	√	√	√	√	√
Endpoint events		√	√	√	√	√	√
Treatment adherence assessment	√	√	√	√	√	√	√

Treatment adherence assessment includes compliance with CPIPB infusion (Weeks 0-2) and long-term standard of care (e.g., offloading, wound care).

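### The two-visit confirmation rule for 12-week healing does not fit the visit schedule: closures first seen at Week 12 have no timely confirming visit, and those first seen at Week 8 have none if "2 weeks apart" is literal

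*Protocol article*

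**What the plan says.** The Primary outcome section fixes the time point: "The primary study end point was the percentage of ulcers in each group achieving 100% healing at 12 weeks". It defines complete healing as full re-epithelialization with no drainage and no need for a dressing, "confirmed at two consecutive visits 2 weeks apart by an independent, blinded wound specialist". It does not say whether the second visit must fall by Week 12 or may come later, and it gives no window around the 2 weeks.

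The Participant timeline lists baseline visits and then "Week 2, Week 4, Week 6, Week 8, Week 12 and year 1". It adds: "Data collection points for specific outcomes are outlined in the schedule of assessments". That schedule, Table 1, has the same columns, with none for Week 10 or Week 14.

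Two other contacts appear in the Control group (SOC) section: "participants will attend regular, scheduled follow-up visits for comprehensive and standardized wound assessment and care", which adds no dates, and "sharp debridement of hyperkeratotic margins and non-viable tissues will be performed weekly by a dedicated, trained wound care podiatrist or nurse as clinically indicated", which is care and is not described as a blinded endpoint assessment.

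The Sample size section states that "the healing rate in the SOC group is approximately 47" per cent, with no time point attached, and that in the pilot "approximately 80% of participants achieved complete wound closure within 12 weeks".

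**The concern.** The article gives both a complete definition of healing and a complete list of visits, and the two cannot be applied together for late closures. This is a conflict between two stated items, not detail left to a fuller document.

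The rule decides who counts as healed in the primary analysis. Followed as written, it scores some ulcers that are closed at Week 12 as failures because no second visit can confirm them. If the site instead arranges unscheduled checks, the result depends on choices that the protocol does not fix, and two analysts could derive different primary results from the same records. Time to healing, a planned time-to-event outcome, has the same difficulty. If late closures are lost, the trial also no longer measures the 12-week rate for which it appears to have been sized.

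**Working it through.** **1. Visit gaps** (Participant timeline and Table 1; year 1 taken as Week 52)

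| Pair | Gap (weeks) | Meets exactly 2 weeks | Meets at least 2 weeks, timely |
|---|---|---|---|
| 2 to 4 | 2 | yes | yes |
| 4 to 6 | 2 | yes | yes |
| 6 to 8 | 2 | yes | yes |
| 8 to 12 | 4 | no | yes |
| 12 to 52 | 40 | no | no |

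The latest first closure that can be confirmed is at Week 6 on the strict reading (exactly 2 weeks) and at Week 8 on the loose reading (at least 2 weeks). Week 12 fails on both. This step needs no assumption about healing rates.

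**2. The plan's own sample size.** Inputs from the Sample size section: 47% vs 80%, one-sided alpha 0.05, power 90%. The formula, with pooled variance under the null and no continuity correction, is

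n = [z(alpha) × sqrt(2p(1−p)) + z(power) × sqrt(p1(1−p1) + p2(1−p2))]² / (p2−p1)², where p = (p1+p2)/2 = 0.635.

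n = [1.645 × 0.681 + 1.282 × 0.640]² / 0.33² = 34.5, so 35 per group. With 10% dropout, 35/0.9 = 38.9, so 39 per group and 78 in total. The stated figure reproduces.

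**3. Countable healing rates. Assumption, not in the documents:** the healing hazard is constant and reaches 47% and 80% at Week 12. Then F(t) = 1 − (1 − F(12))^(t/12).

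- By Week 6: 1 − 0.53^0.5 = 0.272 and 1 − 0.20^0.5 = 0.553.
- By Week 8: 1 − 0.53^(8/12) = 0.345 and 1 − 0.20^(8/12) = 0.658.

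Share of 12-week closures that cannot be confirmed:

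- Strict: 1 − 0.272/0.47 = 42% (control) and 1 − 0.553/0.80 = 31% (CPIPB).
- Loose: 27% and 18%.

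**4. Power.** Power = Φ{[(p2−p1) × sqrt(n) − z × sqrt(2p(1−p))] / sqrt(p1(1−p1) + p2(1−p2))}. The Sample size section is one-sided, while the Secondary outcome analysis section says that all tests are two-sided. That conflict is a separate matter, so both bases are shown, each against its own baseline.

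| Countable rates | One-sided, n=35 | Two-sided, n=35 | Two-sided, n=39 |
|---|---|---|---|
| 47% vs 80% (no loss) | 90% | 83% | 87% |
| 35% vs 66% (loose) | 85% | 76% | 80% |
| 27% vs 55% (strict) | 78% | 67% | 72% |

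**5. Sensitivity to the curve.** If no ulcer heals in the first 2 weeks and the hazard is constant after that, F(t) = 1 − (1 − F(12))^((t−2)/10).

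- Strict: 22% vs 47%, two-sided power 60% (n=35) to 65% (n=39).
- Loose: 32% vs 62%, two-sided power 73% to 77%.

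**6. Patients affected.** First closures after Week 8 and up to Week 12, under the assumption in step 3: 39 × (0.47 − 0.345) + 39 × (0.80 − 0.658) = 4.9 + 5.5, about 10 of 78.

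**The case against.** The strongest reply is that the text is ambiguous rather than impossible. An ulcer closed at Weeks 8 and 12 has been closed at two consecutive visits, and most clinicians would accept that as confirmed. Nor does the Primary outcome section say that the second check must be a Table 1 visit or must fall by Week 12, and a fuller protocol might provide event-triggered confirmation visits. This stands in part: it rules out saying flatly that Week 8 closures cannot count, or that the endpoint is in truth healing by Week 6. It does not help a closure first seen at Week 12, and the article presents its schedule as the place where outcome collection points are set.

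Three stronger inferences are tempting but unsupported.

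- **Confirmation by unblinded staff.** A reader might infer that late closures would be confirmed by staff who know the allocation. The Primary outcome section requires a blinded specialist and blinded photographic adjudication, and nothing permits an unblinded check.
- **Sizing on confirmed 12-week rates.** A reader might take both sizing rates as 12-week figures that this rule then undercuts. Only the 80% is tied to 12 weeks, and the confirmation rule behind either rate is not stated. If both were measured under the same rule and visits, there would be no power loss of this kind.
- **The whole shortfall from 90%.** A reader might set 67% against the planned 90%. Seven points of that gap (90% to 83%) come from the change from one-sided to two-sided testing and do not belong to this point.

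**Conclusion.** The point holds as an internal contradiction between the Primary outcome section and the Participant timeline with Table 1. It is certain for closures first seen at Week 12 and depends on the reading for those first seen at Week 8. It should be corrected, because it determines who counts as healed in the primary analysis.

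The size is illustrative. Like for like, the power loss at 35 per group is about 12 points (strict) or 5 to 6 points (loose) one-sided, and about 16 or 8 points two-sided. These figures rest on the assumed constant hazard and on the two sizing rates not having been measured under the same confirmation rule; the documents settle neither. The contradiction does not depend on either assumption, and the sample size is correct on its own inputs.

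**What to change.** Reconcile the two sections before outcomes are adjudicated:

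- Define 12-week healing as closed at the Week 12 visit and also found closed by the blinded specialist at an adjacent assessment at least 2 weeks before or after. An ulcer closed at Weeks 8 and 12 then qualifies.
- State that confirmation may fall after Week 12.
- Add to Table 1 a Week 14 blinded check (photograph plus inspection), only for ulcers first seen closed at Week 12.
- State that an ulcer that closed earlier but has reopened by Week 12 is not healed at 12 weeks. A definition of closed at or before Week 12 would count it and so change the endpoint.
- Date healing at the first of the two confirming visits, so that time to healing follows the same rule.

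The cost is a short amendment and one brief extra visit for roughly 10 patients on the assumption above (about 13 with the 2-week lag: 6.0 + 7.0). The visit has to be budgeted as new: a healed ulcer needs no dressing, so routine debridement or dressing contacts cannot be relied on to supply it. The sample size calculation need not change for this point, but the source and confirmation rule of the 47% and 80% should be stated.
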